### Framework of ILC

ILC is a type of control engineering that was introduced by Ukiyama [19] in the late 1970s and Arimoto et al [20] in the 1980s. ILC is applied to repetitive processes, where the same tracking task is repeated several times. Examples of traditional application areas of ILC are the control of pick-and-place industrial robots or semiconductor manufacturing [21]. ILC exploits the repetitiveness of processes such as these by learning from past experiences, thus reducing the tracking error over time, as well as adapting to small changes in the processes. An iterative learning controller is able to learn from past experiences by taking the control input and error of previous iterations into account when determining the control input for the next iteration. The typical framework for ILC is

*u_k_*_+1_(∙)=f(*e_k_*_+1_(∙),…,*e_k_*_–_*_s_*(∙),*u_k_*(∙),…,*u_k_*_–_*_r_*(∙)), **(1)**

where *k* is the iteration index, *u* is the control input, and *e* is the tracking error. There are different ways to determine the function *f* in (1). The simplest ILC algorithm is Arimoto et al’s [20] algorithm, where the next control input is equal to the control input plus the scaled error of the previous iteration, that is,

*u_k_*_+1_(*t*)=u_k_(*t*)+*γe_k_*(*t*+1), **(2)**

where *t* is discrete time, and *γ* is a scalar controller parameter. ILC algorithms generally take the form

*u*_k+1_(*t*)=*u*_k_(*t*)+*Ke_k_*(*t*+1), **(3)**

where *K* is the so-called learning-gain operator, which is often based on a model of the system, such as the inverse-model ILC algorithm [22] or the Adjoint algorithm [23]. The algorithms described in (2) and (3) are so-called P-type ILC algorithms as they use the error from previous iterations. Algorithms that use the derivative of the error instead are known as D-type ILC [24].

While ILC was mostly used in industrial and manufacturing processes in its early days, it has found popularity in other application areas, such as stroke rehabilitation [23] or the control of exoskeletons [25] in more recent years.

Since rehabilitation and training, whether physical or cognitive, are inherently repetitive processes, where the task difficulty needs to change progressively, this application area lends itself nicely to the use of ILC.

### Objectives

The primary objective of this study is to accelerate P300-based attention training by progressively and optimally adjusting the task difficulty in a training session to each individual using ILC. The proposed iterative learning controller, which determines the task difficulty based on previous performance and task difficulty level, will be compared to the adaptation algorithm used in a previous study by Arvaneh et al [17]. Thus, we will be able to analyze the replicability of Arvaneh et al’s [17] study. A random task difficulty control group will also be used in this study to compare the training effects of personalized approaches with the training effects due to exposure to a range of nonpersonalized task difficulty levels.

While we expect the cognitive enhancements achieved during the training session to be similar among the groups, we expect the experimental group, where the task difficulty is determined by an iterative learning controller, to complete the training session more quickly than the other groups.

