### Participants

The participants will be healthy individuals aged 18 years or older with no self-reported history of neurological or cognitive illness, and normal or corrected-to-normal vision. Interested participants who do not meet these criteria, have a negative reaction to the electroconductive gel, or who are illiterate will be excluded from the study.

Based on previous work using a P300-based BCI for attention training [17,26], a sample size of 45 participants (15 per group) was determined. Participant recruitment will continue until the sample size is reached. It is expected that around 50 participants will be recruited due to a 10% dropout rate.

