#### RDM Task

The change in performance in the RDM task between pre- and posttraining phases will be analyzed in terms of accuracy and response time. The accuracy is the number of correct trials over the total number of trials, and the response time is the elapsed time between onset of the coherent motion until the correct button is pressed before the end of the coherent motion. The response time of incorrect trials will not be considered. The mean response time will be calculated for each participant individually. Statistical tests, such as ANOVA and paired *t* tests, will be conducted to analyze between-group and within-group differences for both the accuracies and mean response times.

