##### ERP Components

The changes in the ERP components throughout the training will be analyzed. For this purpose, epochs from 150 milliseconds to 550 milliseconds poststimulus onset will be extracted from the EEG data for both target and nontarget trials. Subsequently, the total power across the same centroparietal electrodes as used in [17] (ie, C3, Cz, C4, P3, Pz, and P4) will be calculated for each epoch.

The average total power for all epochs of the calibration and evaluation phases, the training phase, and the after-training phase, respectively, will be calculated. A training-to-calibration ratio of the average power for both target and nontarget trials will be obtained by dividing the average total power during the training phase by the average total power during the calibration and evaluation phases. The same will be done with the average total power during the after-training phase to obtain an after-training-to-calibration ratio.

A ratio of greater than unity indicates an increase in average total power, whereas a ratio of less than unity indicates a decrease in average total power compared to the calibration and evaluation phase. For target trials, an increase in power means that the participant improved their attention, and a decrease in power of nontarget trials can be interpreted as the participant being less distracted by nontarget flashes [17].

Appropriate statistical tests, such as ANOVA, will be conducted to analyze within-group and between-group differences in the aforementioned ratios.

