## Results

This study was approved by the Maynooth University Ethics Committee (BSRESC-2022-2474456) and is registered on ClinicalTrials.gov (NCT05576649). Participant recruitment and data collection began in October 2022. We expect to publish the results in 2023. This study is replicating the experimental protocol of Arvaneh et al [17], comparing their task difficulty adaptation approach to a novel approach using an iterative learning controller, as well as random task difficulty levels in each run.

Arvaneh et al [17] showed a significant enhancement of ERP components and performance in the RDM task after the P300 speller training, suggesting that participants’ attention improved. We expect such an improvement for all groups in this study, with changes in the length of the training between groups due to the different adaptation approaches.

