## Discussion

### Overview

This study aims to evaluate the use of an adaptive P300 speller as a neurofeedback training tool for attention training. We aim to accelerate the training process using ILC and compare personalized and nonpersonalized task difficulty adaptation approaches. By replicating the experimental protocol of Arvaneh et al [17], who demonstrated the adaptive P300 speller’s potential as an easy-to-use and effective neurofeedback training tool, we seek to gather further evidence supporting this application for attention training.

The findings of this study will contribute to the understanding of how different adaptation approaches, both personalized and nonpersonalized, can impact the efficacy of neurofeedback training tools. These insights can guide the design of future BCI-based cognitive training and rehabilitation interventions. Accelerating the training with the P300 speller, without affecting its effectiveness or the users’ frustration levels, will make it a more attractive training option for people with cognitive deficits.

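### Cognitive benefit is expected to be similar across arms, but only difference tests are named for it, and at 15 per arm a non-significant result could not support similarity

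*Protocol article*

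**What the plan says.** The Objectives give acceleration of the training as the primary objective and add an expectation about benefit: "While we expect the cognitive enhancements achieved during the training session to be similar among the groups, we expect the experimental group" to complete the session sooner. The Results section repeats it: "We expect such an improvement for all groups in this study, with changes in the length of the training between groups". The Discussion overview describes what would make the tool attractive: "Accelerating the training with the P300 speller, without affecting its effectiveness".

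For RDM accuracy and response time, the Data Analysis section says: "Statistical tests, such as ANOVA and paired *t* tests, will be conducted to analyze between-group and within-group differences". For the ERP power ratios it says: "Appropriate statistical tests, such as ANOVA, will be conducted to analyze within-group and between-group differences in the aforementioned ratios". The Time-Frequency Analysis section names a one-way ANOVA as its example for the alpha ratios. Training length (total flashes in runs 2-5) is likewise to be compared by a test such as a one-way ANOVA.

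The sample size rests on earlier studies: "Based on previous work using a P300-based BCI for attention training [17,26], a sample size of 45 participants (15 per group) was determined". No significance level, power, effect size, SD, equivalence or non-inferiority margin, or confidence-interval rule is stated.

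**The concern.** The intended message has two parts: ILC training is shorter, and its benefit is preserved. The first is a superiority question, and a difference test suits it. The second is a non-inferiority or equivalence type of statement, and a difference test cannot deliver it. Failing to reject equality means only that no difference was detected, and in a small trial that is a likely outcome even when a sizeable loss exists.

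The within-group paired tests do not fill the gap. Two arms can each improve significantly from baseline and still differ in how much they improve.

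At stake is the interpretation of the shorter session. A session that is shorter but trains less well is a different finding from one that is shorter and trains equally well, and the named methods cannot separate the two when the ANOVA is non-significant.

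**Working it through.** **Inputs.** From the protocol: 15 per arm, three arms, 10% dropout. Assumed, because the protocol gives none: two-sided 5% level, outcome SD of 1 (results are in SD units), one arm worse than the other two by δ, and a pre-post correlation r shown over a range.

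**The plan's own figure.** "It is expected that around 50 participants will be recruited due to a 10% dropout rate": 45 / (1 − 0.10) = 50, which reproduces. The 45 itself cannot be reproduced, since no level, power, effect size or SD is stated.

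**Precision of a pairwise difference.** Half-width = t(0.975, df) × σ × √(2/15), with √(2/15) = 0.365.
- Unadjusted: 2.018 × 1 × 0.365 = 0.74 SD (df 42).
- Baseline-adjusted (ANCOVA), r = 0.6: σ = √(1 − 0.36) = 0.8, so 2.020 × 0.8 × 0.365 = 0.59 SD (df 41).

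An observed difference of exactly zero would therefore still be compatible with a loss of about 0.6 to 0.7 SD under these two assumptions.

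**Chance that the omnibus F test misses a true loss of 0.5 SD.** Noncentrality λ = 15 × δ² × (2/3) / σ². The residual variance σ² is 1 for an unadjusted post-training comparison, 2(1 − r) for change scores and 1 − r² for ANCOVA. Degrees of freedom are 2 and 42 (41 for ANCOVA).

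| Analysis | r | σ² | λ | Power | Missed |
|---|---|---|---|---|---|
| Unadjusted | – | 1 | 2.50 | 26% | 74% |
| Change score | 0.5 | 1 | 2.50 | 26% | 74% |
| Change score | 0.6 | 0.80 | 3.13 | 31% | 69% |
| ANCOVA | 0.6 | 0.64 | 3.91 | 38% | 62% |
| Change score | 0.8 | 0.40 | 6.25 | 57% | 43% |
| ANCOVA | 0.8 | 0.36 | 6.94 | 62% | 38% |
| Change score | 0.9 | 0.20 | 12.5 | 87% | 13% |
| ANCOVA | 0.9 | 0.19 | 13.2 | 89% | 11% |

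For a loss of 0.8 SD, the unadjusted λ is 15 × 0.64 × (2/3) = 6.4, giving 58% power and 42% missed.

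**What margin could 15 per arm support?** For 80% power at zero true difference, with the two-sided 95% CI as criterion, margin ≈ (t(0.975) + t(0.80)) × σ × 0.365.
- Unadjusted: (2.018 + 0.850) × 0.365 = 1.05 SD.
- Adjusted, r = 0.6: (2.020 + 0.850) × 0.8 × 0.365 = 0.84 SD.
- Adjusted, r = 0.9: (2.020 + 0.850) × 0.436 × 0.365 = 0.46 SD.

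A margin equal to the 0.59 SD half-width (adjusted, r = 0.6) would give only about 50% power.

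**The case against.** A reader might infer that the investigators will treat p > 0.05 as proof of similarity. The document does not say so. The Objectives and Results state expectations, the Discussion sentence concerns the attraction of faster training, and no decision rule is given. Looking for between-group differences is legitimate in itself. This stands: the point is that no criterion for similarity is stated, not that a wrong one is.

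The methods are introduced by such as, so ANOVA is an example and not the sole permitted analysis, and a statistical analysis plan that is not shown could add a margin. That also stands. However, every example named is a difference test, and the expectation of similarity and the sample size are fixed in this document with no link between them.

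A reader might also infer that the trial's main comparison fails. It does not. Acceleration is the primary objective, and total flashes in runs 2-5 is a superiority outcome that is untouched by this point.

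Nor is it fully right that a noisier trial is more likely to confirm the expectations. The protocol also expects improvement within every arm, which noise makes harder to show, and its Limitations warn that enhancements may not be significant.

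Finally, the RDM analysis concerns change from before to after training, so unadjusted power is not the only relevant figure. With a strong pre-post correlation the miss rate falls sharply, which is why a range is shown.

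**Conclusion.** The point holds as a mismatch between an expected conclusion and the methods named to reach it. Similar benefit, and acceleration at no cost to effectiveness, cannot be supported by a non-significant difference test with 15 per arm.

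The size depends on the pre-post correlation, which the protocol does not give. A true loss of 0.5 SD would go undetected in roughly 60-75% of trials when the correlation is about 0.6 or lower, in 38-43% at 0.8 and in 11-13% at 0.9. Those figures assume a two-sided 5% level, 15 analysed per arm, and a loss confined to one arm. Even with a high correlation, a non-significant p value would not be the right criterion; the confidence interval would be.

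This is a low-cost improvement to the plan. It does not contradict any figure in it.

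**What to change.** Before any between-arm results are seen:

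1. Name one cognitive outcome for the similarity question, for example RDM mean response time.
2. Report the baseline-adjusted difference, ILC minus control group 1, with its two-sided 95% CI.
3. State that similarity will not be concluded from p > 0.05.
4. Prespecify and justify a margin of loss. Claim that effectiveness is unaffected only if the CI excludes a loss of that size; otherwise report that similarity is not established.
5. Keep total flashes in runs 2-5 as a separate superiority result that does not depend on step 4.

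The cost is analysis wording and one confidence interval; no new data are needed. The drawback is that at this size the similarity question will often be inconclusive. With 80% power at zero true difference, the margin would have to be about 0.84 SD (adjusted, correlation 0.6) to 1.05 SD (unadjusted). The margin should be justified by what loss would matter, not widened to suit the sample size.

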## Methods

### Study Design

In this single-blind, 3-arm randomized controlled trial with parallel-arm design, the effectiveness of different task difficulty adaptation approaches in a P300 speller task will be evaluated and compared. The study involves a single experimental session that lasts no longer than 2 hours (including setup). The experiments will be conducted in an electrically shielded, dark, and quiet room on the Maynooth University campus.

### Recruitment

The participants for this study will be recruited from the staff and student community of Maynooth University through an open enrollment process. Study participants will be alerted to the study through advertisement flyers distributed throughout the Maynooth University campus and through email advertisements sent to staff and students.

### Participants

The participants will be healthy individuals aged 18 years or older with no self-reported history of neurological or cognitive illness, and normal or corrected-to-normal vision. Interested participants who do not meet these criteria, have a negative reaction to the electroconductive gel, or who are illiterate will be excluded from the study.

Based on previous work using a P300-based BCI for attention training [17,26], a sample size of 45 participants (15 per group) was determined. Participant recruitment will continue until the sample size is reached. It is expected that around 50 participants will be recruited due to a 10% dropout rate.

### Ethical Considerations

This study was approved by the Maynooth University Ethics Committee (BSRESC-2022-2474456) and is registered on ClinicalTrials (NCT05576649). Interested participants who meet the eligibility criteria and give informed consent to study participation, allowing the recording of their performance in the training session and their brain signals, as well as the use of the collected data for this study and future research, will be invited to conduct a patch test to mitigate the risk of allergic reactions to the electroconductive gel. Participants will be advised that they have the freedom to withdraw from the experiment at their discretion at any time throughout the course of the experiment and will not be compensated for their participation in the study. The data from this study will be irreversibly anonymized immediately upon collection.

### Procedure

The experimental procedure of this study is based on previous work by Arvaneh et al [17]. An overview of the procedure can be found in Figure 1.

Participants will be asked to fill in a questionnaire at the beginning and end of the experiment. They will then complete a continuous random dot motion (RDM) task, which will serve as a baseline for their cognitive abilities. Afterward, participants will receive attention training using a P300 speller task, where the task difficulty in each run of the speller is either chosen randomly (control group 2) or adjusted to the participant’s performance (control group 1 and experimental group). To analyze improvements in cognitive abilities, participants are asked to complete the RDM task again after the training.

**Figure 1 figure1:**
[figure not shown]
Study procedure based on Arvaneh et al [17]. ILC: iterative learning control.

### EEG Data Acquisition

Participants’ EEG data will be recorded during the P300 speller training phase of the experiment. EEG data will be collected using the battery-operated ANT Neuro eego rt [27] with a 32-channel waveguard cap [28]. The sintered silver–silver chloride electrodes are located in standard 10-20 positions. Impedances will be maintained below 5 kΩ during recording.

The EEG signals will be acquired in the OpenViBE software [29] at a sampling rate of 500 Hz. All channels will be band-pass filtered (1-20 Hz) and down-sampled by a factor of 4 before further processing.

Offline analysis of the EEG data will be carried out in MATLAB [30] using the EEGLAB toolbox [31]. Since this study is a replication of Arvaneh et al’s [17] study, the following offline analysis steps closely follow the steps described in the study. The continuous EEG signals will be rereferenced to Fz, band-pass filtered between 0.5 and 35 Hz and separated into baseline-corrected epochs of 150 milliseconds before the stimulus to 550 milliseconds post stimulus, where the 150 milliseconds prestimulus period is used as the baseline. Epochs with an amplitude of more than 75 µV or those with a voltage step of more than 150 µV within a 200-millisecond window will be excluded from analysis.

### Tasks and Stimuli

#### Questionnaire

Participants will be asked to complete the same 10-point Likert scale questionnaire as in Arvaneh et al [17]. It consists of the four questions: (1) How tired are you now? (2) How alert do you feel? (3) How bored do you feel? (4) Do your eyes feel tired?

This questionnaire will be completed at the beginning and end of the experiment so that responses before and after training can be compared.

In addition, the NASA Task Load Index will be used at the end of the experiment to assess participants’ perceived workload of the training [32].

#### RDM Task

The continuous RDM task is based on Arvaneh et al [17] and Kelly and O’Connell [33]. In this task, the participants will focus on moving dots on the screen, which transition from incoherent motion to coherent motion. During incoherent motion, all dots will continuously move in random directions, whereas in coherent motion, a significant fraction of the dots will move in one direction, either left or right. The participants will be asked to indicate the direction of the coherent motion by pressing the left or right arrow key once they are sure of the motion direction. In both the pre- and posttraining phases, the main task consists of 40 trials, where the coherence level, that is, the fraction of coherently moving dots, and the motion direction vary in each trial.

An average of 118 dots, with a size of 6×6 pixels each, are displayed in a circular aperture of 5° at a viewing distance of 70 cm, resulting in a dot density of approximately 10.8%. Each dot is black against a grey background. The dots are moving at a speed of 3.33°/second. The incoherent motion lasts for either 3.1, 4.2, or 5.7 seconds, and the coherent motion always lasts for 1.9 seconds. The coherence level is either 19% or 25%.

To allow participants to understand the task, a practice session will be carried out before the pretraining phase. The practice session consists of 3 blocks of 6 trials each. In the first block, the coherence levels are either 60% or 80%, reducing to 30% or 40% in the second block, and finally reaching 20% or 25% in the last block of the practice session. All other parameters of the task are the same as above. During the practice session, participants will receive verbal feedback on hits, misses, and false alarms.

The code for this task was developed in-house using PsychoPy [34] and the stimuli are presented on a 52.7-cm-wide LED monitor with a refresh rate of 60 Hz and a resolution of 1920×1080 pixels.

#### P300 Speller Task

##### Overview

In this study, the P300 speller implementation in OpenViBE [29] is used. This P300 speller uses the xDAWN algorithm [35] to train a spatial filter that enhances the SNR of the P300 ERPs. This reduces the 32 EEG channels to 3 components, which are weighted combinations of all channels. A linear discriminant analysis classifier is used to distinguish target and nontarget trials. It should be noted that the row and column with the highest probability of belonging to the target class are chosen, even if that is below 50%. Both the spatial filter and classifier are trained for each participant using calibration data.

Figure 2 shows the 6 by 6 grid of letters and numbers that is displayed on the screen. The word to be copy-spelled and the identified symbols can be seen below the grid. If the identified symbol is the same as the target symbol, it will be displayed in green. If the identified symbol is in the same row or column as the target symbol, it will be displayed in orange and if it is wrong, it will be displayed in red.

Outside of the training phase, 12 flashes per row and column are used. Each flash lasts 55 milliseconds with an interflash interval of 117 milliseconds. Each target symbol is highlighted in blue for 6 seconds before the flashing begins.

In each run after the calibration phase, the spelling accuracy, that is, the fraction of symbols that were identified correctly, is calculated for all numbers of flashes between 1 and the actual number of flashes used.

